#### Handling of missing data

Multiple imputation or model-based methods will be used to address missing values, assuming data is missing at random.Sensitivity analyses will be performed to assess the impact of missingness on model accuracy and prediction.

#### Software:

Statistical analyses will be performed using R, Python (scikit-learn, TensorFlow), and SPSS, as applicable.

#### Reference to statistical analysis plan (SAP)

A detailed statistical analysis plan (SAP), including model selection criteria, tuning parameters, and subgroup analysis strategies, is maintained as a separate document by the data science team at MANIT Bhopal and is available upon request.

### Interim analyses {21b}

No interim analyses are planned as the study is non-interventional. However, AI model development will occur iteratively after each follow-up phase to refine predictive accuracy.

### Methods for additional analyses (e.g., subgroup analyses) {20b}

The study includes planned subgroup analyses and adjusted analyses to enhance model performance interpretation and to explore differential effects across population segments.

#### Subgroup analyses

The following predefined subgroups will be analyzed to assess variability in myopia progression and predictive model performance:Age groups: 6–10 years, 11–14 years, 15–18 yearsGeographic location: Urban vs. rural participantsGender: Male vs. femaleBaseline myopia status: Myopic vs. non-myopic at enrolment. Parental myopia: Present vs. absent

Subgroup analyses will involve stratified modeling and comparative evaluation of outcome trends using interaction terms within regression models.

#### Adjusted analyses

Multivariable regression models (e.g., linear or logistic regression for continuous or categorical outcomes, respectively) will be adjusted for potential confounders including:AgeGenderScreen timeDuration of outdoor activitySocio-economic statusParental myopia

These adjustments aim to isolate the effect of independent predictors on myopia progression and improve the interpretability and generalizability of AI-based predictions.

#### Model sensitivity and robustness checks

Internal cross-validation (e.g., k-fold) and bootstrapping will be performed.Sensitivity analysis will test the impact of varying thresholds for clinically significant myopia progression (e.g., ≥ –0.50 D/year vs. ≥ –1.00 D/year).Sub-models excluding outliers or high-leverage data points will be analyzed to assess stability.

These additional analyses will support the rigor, reproducibility, and real-world applicability of the developed AI model.

### Methods in analysis to handle protocol non-adherence and any statistical methods to handle missing data {20c}

#### Analysis population

All participants enrolled and assessed at baseline will be included in the intention-to-observe population, which includes:All participants with complete baseline demographic and ocular data All participants selected for longitudinal follow-up, regardless of the number of follow-up assessments completed

There is no randomization or treatment allocation; hence, conventional “per-protocol” or “as-randomized” classifications do not apply. However, for robustness, analyses will distinguish between:Full analysis set (FAS): All eligible participants with at least baseline dataComplete-case analysis set (CCAS): Subset of participants with complete data at all scheduled time pointsLongitudinal analysis set: All participants in the follow-up cohort with at least one post-baseline visit

#### Handling of missing data

To address potential loss to follow-up and incomplete entries:Descriptive statistics will be used to assess the extent and pattern of missingness (MCAR, MAR, or MNAR)If data are assumed missing at random (MAR):oMultiple imputation will be used for demographic, behavioral, and ocular parametersoImputation models will incorporate all relevant covariates to preserve statistical power and reduce biasIf data are not missing at random (MNAR):oSensitivity analyses will be conducted using worst-case and best-case scenariosoMissingness indicators may be included as covariates in predictive models

All imputed datasets will be pooled using Rubin’s rules, and imputation diagnostics will be documented as part of the statistical analysis plan.

### Plans to give access to the full protocol, participant level-data and statistical code {31c}

The research team is committed to transparency and knowledge dissemination in accordance with national and international research ethics standards.Full Protocol: A de-identified version of the final approved study protocol will be made publicly available via institutional repositories or published as a supplementary file alongside the primary results manuscript.Participant-Level Dataset: De-identified, aggregated participant-level data may be made available for academic research purposes upon reasonable request to the Principal Investigator, subject to approval by the Institutional Ethics Committee (IEC) at AIIMS Bhopal and execution of a formal data-sharing agreement. No identifiable personal data will be shared under any circumstances.Statistical Code and Algorithms: Statistical scripts and model code (e.g., for machine learning and AI-based prediction algorithms) developed during this study will be shared through open-access repositories such as GitHub or Zenodo following publication of primary results, where feasible and in compliance with institutional policies.

## Oversight and monitoring

### Composition of the coordinating centre and trial steering committee {5d}

The TSC will meet quarterly throughout the duration of the study (36 months), with additional meetings as needed.

The data team will coordinate with the AIIMS team on a monthly basis and as required during key model deployment phases.

Coordinating centerThe coordinating center for the trial is based at the Department of Ophthalmology, All India Institute of Medical Sciences (AIIMS), Bhopal. This center is responsible for the day-to-day management and operational execution of the study. Core responsibilities include:Participant enrolment coordination and school liaisonTraining and deployment of field data collection teamsOversight of informed consent, data collection, and clinical evaluationsLogistics planning for school visits and follow-upsThe coordinating centre will meet bi-weekly during the first 6 months of enrolment and monthly thereafter, with emergency meetings convened as required.Trial Steering Committee (TSC)The Trial Steering Committee will provide overall scientific oversight and strategic direction. It will consist of senior clinical investigators, biostatisticians, and external advisors. Key responsibilities include:Reviewing trial progress and protocol adherenceAdvising on protocol amendments if necessaryMonitoring recruitment, data completeness, and safety concernsApproving major publications or data sharingData Management and AI Modelling TeamThis team, based at Maulana Azad National Institute of Technology (MANIT), Bhopal, is responsible for:Development and maintenance of the data capture platformData cleaning, validation, and database locking proceduresAI model training, testing, and performance evaluationMaintaining data security and compliance with SOPsEndpoint adjudication and clinical review committeeA panel of ophthalmologists from AIIMS Bhopal will serve as the clinical adjudication team to:Verify clinical classifications of myopia and progression statusReview and confirm key ocular measurements flagged by automated systemsResolve discrepancies or borderline casesThe adjudication committee will convene biannually or upon review of a substantial batch of flagged data.Ethics and regulatory oversightThe Institutional Ethics Committee (IEC) at AIIMS Bhopal provides independent oversight. All major amendments, safety concerns, and reports will be submitted to the IEC in compliance with regulatory requirements.

### Composition of the data monitoring committee, its role and reporting structure {21a}

Given the non-interventional and minimal-risk nature of this observational cohort study, which does not involve clinical treatments or investigational drugs/devices, a formal independent Data Monitoring Committee (DMC) has not been constituted.

#### Justification for not establishing a DMC

The study involves non-invasive, routine ophthalmic assessments and questionnaire-based data collection.No investigational product, therapeutic intervention, or random allocation is involved.The trial poses no foreseeable risks beyond standard visual screening procedures.Adverse event monitoring in the traditional sense is not applicable.

#### Internal oversight provisions

To maintain data quality and ethical integrity, internal oversight will be ensured through:Monthly internal data reviews by the data coordination team at MANIT Bhopal and AIIMS BhopalQuarterly reporting to the Trial Steering Committee (TSC), which includes independent academic and clinical advisorsRegular updates and compliance reporting to the Institutional Ethics Committee (IEC) at AIIMS Bhopal

These mechanisms are deemed adequate for ensuring participant safety, data reliability, and protocol adherence in this observational, low-risk study context.

### Adverse event reporting and harms {22}

An independent Clinical Safety Oversight Subcommittee under the Trial Steering Committee (TSC), comprising senior clinicians not involved in routine data collection, will review all adverse events. Serious adverse events (SAEs) will be reviewed within 48 h and reported to the Institutional Ethics Committee (IEC) as per regulatory timelines. The committee will oversee causality assessment, ensure timely medical or surgical management at AIIMS Bhopal if required, and document all actions in the Trial Master File.

#### Nature of study and risk profile

This study is strictly observational and involves non-invasive ophthalmic assessments, questionnaires, and biometric measurements. No investigational products, therapeutic interventions, or invasive procedures are administered. As such, the anticipated risk to participants is minimal.

#### Adverse event monitoring plan

While adverse events (AEs) are not expected, the study team has established a system for the collection, assessment, and reporting of any solicited or spontaneously reported events that may arise in connection with study procedures, including but not limited to:Allergic reactions or discomfort associated with cycloplegic eye drops, if usedPsychological discomfort or anxiety in younger children during assessmentsUnforeseen events related to data collection logistics (e.g., injury during on-site visit)

#### Collection and documentation

Any untoward occurrence observed or reported by participants, parents, or school authorities during or immediately following data collection will be recorded in the Adverse Event Log, maintained by the site coordinator at AIIMS Bhopal.A trained ophthalmologist will evaluate the event and document the nature, severity, onset, outcome, and relatedness to study procedures.

#### Reporting and escalation

All serious adverse events (SAEs), although unlikely, will be reported to the Institutional Ethics Committee (IEC) at AIIMS Bhopal within 24 h, followed by a detailed report within 7 days.The Principal Investigator will also notify the Trial Steering Committee during the next scheduled review, or immediately if the event is safety–critical.

#### Management and compensation

Participants requiring follow-up care due to any AE deemed study-related will be referred to the Department of Ophthalmology at AIIMS Bhopal.Compensation, if applicable, will be provided in accordance with national ethical guidelines (ICMR 2017) and institutional policy.

### Frequency and plans for auditing trial conduct {23}

Although this is a minimal-risk, observational cohort study, periodic internal audits will be conducted to ensure protocol compliance, data integrity, and adherence to ethical and regulatory standards.

#### Outcome

Audits will be conducted quarterly throughout the 36-month study period and may be repeated more frequently if significant protocol deviations, safety concerns, or data inconsistencies are identified. Follow-up (re-audit) visits will be performed to verify implementation of corrective and preventive actions (CAPA), where applicable.

#### Audit frequency and scope

Quarterly internal audit**s** will be conducted throughout the study period.These audits will include a review of:oInformed consent documentationoParticipant enrolment logs and eligibility complianceoData collection completeness and accuracyoAdverse event logs (if any)oData storage and confidentiality procedures

#### Audit procedures

Audit checklists will be developed in accordance with the approved protocol and Good Clinical Practice (GCP) guidelines.Each audit will include a random review of 10–15% of participant records.Discrepancies or protocol deviations, if identified, will be documented, addressed, and reported to the Principal Investigator and Trial Steering Committee.

#### Independence:

Audits will be conducted by a designated quality assurance team from AIIMS Bhopal’s Research Oversight Unit, who are not directly involved in the day-to-day conduct of the study.These auditors are independent from the study investigators and the funding body, ensuring objectivity in monitoring compliance.

All audit findings and corrective actions will be documented in the Trial Master File (TMF) and will be made available to the Institutional Ethics Committee upon request.

### Plans for communicating important protocol amendments to relevant parties (e.g. trial participants, ethical committees) {25}

Any significant changes to the study protocol—including modifications to eligibility criteria, outcome measures, data collection methods, statistical analysis plans, or study timelines—will be formally documented, justified, and communicated to all relevant stakeholders in a timely and transparent manner.

#### Scope of amendments covered

Changes in study objectives or endpointsAdjustments in participant eligibility criteriaModifications to data collection tools, timing, or proceduresUpdates to statistical methods or analysis populationsChanges in site locations, study duration, or sample size

#### Notification and approval process

Principal Investigator (PI):Responsible for initiating and documenting any proposed amendment with justification.Institutional Ethics Committee (IEC):All protocol amendments will be submitted to the IEC at AIIMS Bhopal for review and approval prior to implementation, in accordance with national ethical regulations.Trial Steering Committee (TSC):Amendments will be presented to the TSC for advisory input and oversight.Trial Registry:The trial registration entry on the Clinical Trials Registry of India (CTRI) or equivalent registry will be updated to reflect approved amendments, including changes in outcomes, methodology, or sponsor-related details.Participating Institutions and Investigators:All study staff, including data collectors and site coordinators, will receive formal written communication outlining the approved changes along with training (if needed) to ensure implementation fidelity.Participants (if applicable):In cases where the amendment directly affects participants’ rights, safety, or participation (e.g., changes in follow-up procedures or data usage), updated informed consent will be sought.Publications and Sponsors:Journals, regulatory authorities (if applicable), and the funding agency (ICMR) will be notified of significant amendments at the time of submission or reporting.

### Dissemination plans {31a}

The investigators are committed to transparent, timely, and responsible communication of trial outcomes to all relevant stakeholders, including participants, the scientific community, healthcare professionals, policymakers, and the general public.

#### Communication to participants and schools

Summary results will be shared with participating schools and parents/guardians via printed infographics or community reports written in clear, age-appropriate language.School-based dissemination events may be organized to explain the findings and their implications for student eye health and preventive strategies.

#### Scientific and professional dissemination

The trial results will be submitted for publication in peer-reviewed open-access journals and presented at national and international ophthalmology, optometry, and public health conferences.Authorship will follow the ICMJE guidelines, and there are no publication restrictions imposed by the sponsor (ICMR).

#### Public access and registry reporting

Summary results will be uploaded to the Clinical Trials Registry–India (CTRI) upon study completion, as per regulatory requirements.De-identified datasets, statistical code, and key findings may be made publicly available in open-access repositories (e.g., Zenodo, GitHub) in compliance with institutional policies and ethical approvals.

#### Policy and healthcare outreach

Findings relevant to public health policy (e.g., screen-time guidelines, school eye screening protocols) will be shared with health authorities, NGOs, and educational boards to facilitate evidence-based interventions.

All dissemination efforts will respect participant confidentiality, ethical obligations, and intellectual property rights, and will aim to promote equitable access to study insights.

## Discussion

This study aims to address a significant and growing public health concern in India—the progression of myopia among school-going children—by developing an artificial intelligence–enabled predictive model based on longitudinal ocular and behavioral data. While the study is observational in nature and non-interventional, its scale, setting, and technological scope present several practical and operational challenges that merit consideration.

One of the primary logistical challenges lies in the school-based implementation of the study, which requires extensive coordination with educational institutions across both urban and rural areas in the Bhopal division. Securing administrative permissions, aligning data collection with academic calendars, and minimizing classroom disruption while maintaining compliance with ethical procedures (such as obtaining parental consent) are key operational priorities. The research team has incorporated several mitigation strategies, including liaison officers, institutional engagement workshops, and flexible scheduling of school visits.

The large-scale data collection effort, involving clinical ophthalmic measurements and behavioral questionnaires from 10,000 to 12,000 children, necessitates strong data management infrastructure. The use of real-time, tablet-based electronic data capture platforms with built-in validation rules addresses many quality assurance issues; however, variable internet access and field conditions may pose occasional risks to seamless data syncing and backup. Furthermore, standardization of measurements—especially cycloplegic refraction and axial length—is essential to model accuracy and will be supported by strict training protocols, inter-observer reliability checks, and central quality audits.

A significant challenge anticipated in the longitudinal phase is participant retention over the 24-month follow-up period. Migration, school dropouts, or parental withdrawal of consent may contribute to loss to follow-up. The study incorporates multiple strategies to mitigate this, including SMS reminders, parent-teacher engagement, and tracking systems to maximize follow-up compliance. Nevertheless, missing data remains a possibility and will be addressed through statistical techniques such as multiple imputation and sensitivity analyses [9, 10].

Conducting research in school-based settings may present practical challenges, including coordination with academic schedules, variability in parental consent return rates, and potential loss to follow-up due to student transfers or absenteeism. These challenges will be addressed through advance institutional coordination, flexible scheduling, structured parent engagement strategies, and systematic follow-up reminders to ensure minimal disruption and sustained participation [11, 12].

From a technological standpoint, developing and validating machine learning models that are both accurate and interpretable in a public health context is inherently complex. The study team has committed to using explainable AI approaches to ensure clinical utility and user trust. Another concern involves the ethical handling of large-scale, identifiable data from minors. The study has been designed in compliance with institutional and national data protection standards, with strict access controls and de-identification procedures in place. 

In conclusion, while the proposed study presents certain logistical and methodological complexities, its design incorporates structured mitigation strategies and oversight mechanisms. The integration of AI with epidemiological field research holds promise for scalable, evidence-based solutions to pediatric eye health challenges in low-resource settings.

## Trial status

Protocol Version: Version 1.0Date of Finalization: 16 July 2025Date Recruitment Began: 01 August 2025Expected Completion of Recruitment: 31 March 2026

The recruitment timeline reflects the logistical considerations of conducting school-based data collection across multiple urban and rural sites in the Bhopal division. Follow-up assessments will continue for up to 24 months post-enrolment of the last participant.

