### Outcomes {12}

#### Primary outcome

Measurement Variable: Risk of myopia progressionAnalysis Metric: Change in spherical equivalent refraction (SER) and axial length over timeMethod of Aggregation: Mean change from baseline to each 6-month follow-up, stratified by age group, urban/rural location, and baseline refractive statusTime Points: Baseline, 6 months, 12 months, 18 months, and 24 monthsClinical Relevance**:** Monitoring SER and axial elongation is clinically validated as the gold standard for quantifying myopia progression. Accurate prediction supports early intervention and reduces the risk of long-term complications such as retinal detachment and macular degenerationThe AI model performance metrics (e.g., AUROC, sensitivity, specificity) will be evaluated against the primary clinical outcome of myopia progression (change in spherical equivalent refraction and axial length), thereby linking predictive accuracy directly to clinically meaningful disease progression

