**Schematic diagram of study timeline**

**Table Tabb:** 

Study period	Enrolment	Baseline (T0)	Follow-up 1 (T1)	T2	T3	T4
Time point (months)	0–3	2–9	18	24	30	36
Informed consent	✔					
Eligibility assessment	✔					
Demographic data		✔				
Ocular examinations		✔	✔	✔	✔	✔
Questionnaire		✔	✔	✔	✔	✔
AI model training		✔	✔	✔	✔	✔
Mobile App testing					✔	✔

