## Statistical methods

### Statistical methods for primary and secondary outcomes {20a}

#### Primary outcome analysis

Objective: To quantify and predict myopia progression over time based on spherical equivalent refraction (SER) and axial length measurements.Approach:oDescriptive statistics (mean, standard deviation) will be used to report baseline characteristics.oLinear mixed-effects models will be applied to assess longitudinal changes in SER and axial length over follow-up periods, accounting for repeated measures and potential confounders (e.g., age, screen time, parental myopia).oTime-to-event analysis (e.g., Kaplan–Meier estimates) may be used to assess time to clinically significant myopic progression (e.g., ≥ –0.50 D/year), if applicable.

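### The primary time points labelled 6, 12, 18 and 24 months fall 9–16, 15–22, 21–28 and 27–34 months after baseline on the protocol's own schedule, and the calendar sections do not agree

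*Protocol article*

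**What the plan says.** Under Outcomes {12}, Primary outcome, the aggregation is "Mean change from baseline to each 6-month follow-up", and the listed time points are baseline and 6, 12, 18 and 24 months. The section on follow-up assessments likewise describes six-monthly visits for 24 months.

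Participant timeline {13} works in study months. Phase 1 has enrolment and consent in Months 1–3 and the baseline ocular assessment in Months 2–9. Phase 2 has cohort selection in Month 13 and Visits 1 to 4 at Months 18, 24, 30 and 36. The schedule table agrees: its time row reads "Time point (months) 0–3 2–9 18 24 30 36", for enrolment, T0 and T1 to T4. Its ocular-examination row has no entry between T0 and T1.

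Trial status gives recruitment from 1 August 2025 to an expected end on 31 March 2026, and adds: "Follow-up assessments will continue for up to 24 months post-enrolment of the last participant".

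Statistical methods {20a} specifies linear mixed-effects models for the longitudinal changes without defining the time variable. It adds an optional analysis of "time to clinically significant myopic progression (e.g., ≥ –0.50 D/year"). The robustness checks under {20b} vary that threshold between 0.50 and 1.00 D/year.

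**The concern.** A change from baseline can be read only if the time since baseline is known. Here the labels on the primary outcome do not match the schedule that will produce the data. No child seen on schedule can have a 6-month change from baseline, because the shortest possible first interval is 9 months.

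Three things are at stake:

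- **The reported primary outcome.** A mean change published as a 6-month change would be a change over 9 to 16 months, however well it was modelled. Model performance is to be judged against the same progression outcome, so the stated prediction horizon would be wrong too.
- **Comparability between children.** The baseline window adds a 7-month spread in elapsed time that depends on when a child was examined.
- **Any annual rate measured from baseline.** If the label is used as the divisor, the rate is too large, most of all at the first visit.

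The calendar sections also give different enrolment periods and, on one reading, different ends of follow-up. The schedule therefore cannot be settled by looking elsewhere in the document.

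**Working it through.** **Inputs.** Labels 6, 12, 18 and 24 months (Outcomes {12}). Baseline examination in Months 2–9; visits at Months 18, 24, 30 and 36; cohort selection in Month 13 (Participant timeline {13} and its table). Recruitment dates and the follow-up limit (Trial status). Threshold 0.50 D/year ({20a}, {20b}).

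**Step 1: can the labels be reproduced?** Only with a clock started at Month 12: 18−12 = 6, 24−12 = 12, 30−12 = 18, 36−12 = 24. Starting at cohort selection (Month 13) gives 5, 11, 17 and 23. No eye examination is scheduled at either point.

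**Step 2: elapsed time from the scheduled baseline.** Elapsed time = visit month − baseline month, with baseline from Month 9 (shortest) to Month 2 (longest). Factor = elapsed time / label.

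| Visit | Label | Elapsed time (months) | Factor if the label is the divisor |
|---|---|---|---|
| 1 (Month 18) | 6 | 18−9 = 9 to 18−2 = 16 | 1.50–2.67 |
| 2 (Month 24) | 12 | 15 to 22 | 1.25–1.83 |
| 3 (Month 30) | 18 | 21 to 28 | 1.17–1.56 |
| 4 (Month 36) | 24 | 27 to 34 | 1.13–1.42 |

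Counting the edges of the months widens each interval by about one month at each end.

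**Step 3: spread between children.** For two children with the same constant rate, the observed change at Visit 1 can differ by a factor of 16/9 = 1.78, and at Visit 4 by 34/27 = 1.26.

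**Step 4: effect on a rate, if labels were used.** Assume a constant true rate of 0.50 D/year.

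- Visit 1: 0.50 × 1.50 = 0.75 to 0.50 × 2.67 = 1.33 D/year.
- Visit 4: 0.50 × 1.125 = 0.56 to 0.50 × 1.417 = 0.71 D/year.
- Least-squares slope through all five points on label time: 0.55 D/year (baseline in Month 9) to 0.67 D/year (baseline in Month 2).
- True rate that would reach 0.50 D/year at Visit 1: 0.50 × 6/16 = 0.19 to 0.50 × 6/9 = 0.33 D/year.

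Visits 1 to 4 are 6 months apart (24−18, 30−24, 36−30), so rates between those visits are unaffected.

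**Step 5: the calendar.** August 2025 to March 2026 is 8 months, against Months 1–3 in the timeline. The protocol does not date Month 1, so the follow-up limit is shown under alternatives.

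| Meaning of the last enrolment | Its month | Plus 24 | Against Visit 4 (Month 36) |
|---|---|---|---|
| 31 March 2026, Month 1 = August 2025 | 8 | 32 | 4 months short |
| 31 March 2026, Month 1 = July 2025 | 9 | 33 | 3 months short |
| End of Months 1–3 | 3 | 27 | before Visits 3 and 4 |
| Entry to the Phase 2 cohort | 13 | 37 | Visit 4 covered |

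**The case against.** The strongest reply is that no bias has been shown. The protocol never says that change will be divided by label time. The time variable in the mixed models is undefined, and its coding is ordinary content for the separate analysis plan, which the protocol says exists and which is not at hand. Actual dates would remove the error from the slopes. The primary metric is a mean change, not an annual rate; D/year appears only as an example threshold in an optional analysis and in a sensitivity analysis. All of this stands. A reader might infer that the trial's progression rates are overstated, or that every rate is inflated. The document supports neither: the first depends on an analysis that it does not specify, and rates between Visits 1 and 4 are sound in any case. The 0.19–0.33 D/year figures illustrate the risk and do not describe a planned classification.

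A second reply concerns the calendar. A reader might infer that follow-up must end at Month 32. That assumes that Month 1 is August 2025 and that enrolment means Phase 1 enrolment. Recruitment {15} also speaks of enrolling the children selected for follow-up. On that reading the limit is Month 37 and there is no conflict with Visit 4. With Month 1 in July 2025, the recruitment dates also coincide with the baseline window of Months 2–9. This stands too: the end of follow-up is ambiguous, not contradictory under every reading.

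A third point is that field teams are to work in several districts simultaneously. That may limit any link between examination date and location, but it does not narrow the 7-month window.

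None of these replies repairs the labels on the primary time points, or the three-month enrolment window set against eight months of recruitment.

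**Conclusion.** The point holds as an internal inconsistency in the time axis of the primary outcome. On the protocol's own schedule the four labelled time points are 9–16, 15–22, 21–28 and 27–34 months after baseline. This rests only on the stated months and on the absence of any scheduled examination between Month 9 and Month 18.

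The effect on rates is conditional. If a change-from-baseline rate used the labels, it would be too large by 1.5–2.7 times at Visit 1, falling to 1.1–1.4 times at Visit 4. If actual dates are used, the slopes escape this error, but a summary reported as a 6-month change would still be misnamed.

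On the calendar, the enrolment conflict is plain. The end of follow-up falls short of Visit 4, at about Month 32–33, only if Trial status refers to Phase 1 enrolment ending on 31 March 2026. The wording needs settling whichever reading was meant.

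**What to change.** 1. Reconcile Outcomes {12}, Participant timeline {13} with its table, and Trial status to one calendar. State which date is Month 1, which enrolment period applies, and whether the follow-up limit runs from Phase 1 enrolment or from entry to the Phase 2 cohort.
2. Relabel the primary time points with the intervals that the reconciled schedule gives, or re-define the baseline so that the labels are true.
3. State that time in the mixed models, and in every D/year rate, is actual time from each child's own baseline examination date.
4. Confirm that the electronic case report form records the date of each examination. The protocol describes the forms and the variables but does not mention this date, so it should not be taken as given.

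Items 1 to 3 cost protocol wording, a registry update if the registered time points change, and a matching sentence in the analysis plan. Item 4 is a check, or one added field if the date is missing; dates for examinations already done would then have to be recovered from field records. Re-defining the baseline would cost more if it meant a further examination. All of this should be settled before any follow-up data are analysed.
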